### Case status

*WTC-AHR* will be defined as having a positive methacholine (PC_200_ < 16), or a positive bronchodilator response (by ATS/ERS guidelines with improvement of FEV_1_ by 12% and at least 200 mL) at least once post-9/11 [73, 74] and/or EMR diagnosis. *GERD* will be defined as: biopsy-proven erosive esophagitis LA grade C or D; stricture or Barrett’s esophagus on endoscopy; and/or esophageal acid exposure time > 6% on a pH or pH impedance study. GERD will also be defined on EMR diagnosis and/or PPIs, H_2_ blockers, antacid, or surface agent use [75]. *BE*, as a subset of GERD, will have any of the following additional inclusion criteria: biopsy-proven columnar epithelium lining ≥ 1 cm of the distal esophagus with intestinal metaplasia characterized with goblet cells on histology; diagnosis on EMR, Tables 2 and 3 [75]. The recruited participants will be consented prior to any research activity and measurement visit via REDCap software or in person.

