The diagnosis of GERD itself is a complex process that relies on subjective clinical symptoms and often necessitate objective but invasive testing such as endoscopy and 24-h pH monitoring [66]. Those with endoscopic evidence of reflux may be entirely asymptomatic, potentially leading to under-diagnosis of patients at risk of BE and EAC [67, 68]. Even with the most invasive procedures, the diagnosis of GERD can be elusive and plagued by poor sensitivity [69].

In light of this, we propose to explore noninvasive biomarkers that could identify a population of aerodigestive disease, enabling better phenotyping of FDNY-WTC cohort with aerodigestive disease. In addition to their diagnostic utility, noninvasive biomarkers may direct future research into mechanisms and their downstream effects. GERD/BE biomarkers are also important to identify in the clinically silent presentations [69]. Additionally, we will identify novel non-invasive biomarkers of aerodigestive disease through a multi-OMIC approach. We will profile not only the metabolome and microbiome, but also exhaled, secreted, and blood biomarkers of aerodigestive disease Fig. 1 [70].

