**Fig. 2 Fig2:**
[figure not shown]
Study design

*Recruited Cohort* will be developed to assess for noninvasive biomarkers. We will recruit a subset *N =* 40/group (*i.* AHR only *ii.* GERD only *iii.* BE *iv.* GERD/BE and AHR overlap or *v.* No GERD nor AHR) from the sub-cohort, Fig. 2. Recruitment strategies will include: i. Direct mailings; ii. Email (potential participants will be sent the same IRB-approved recruitment message to their personal emails using end-to-end encryption; iii. Study website will include recruitment messages providing general information on the study and answers to frequently-asked questions. No direct communications will be made with participants through the website, and no PHI will be used or available within the study website; iv. Telephone contact. A description of the study will be provided to potential participants and, upon their expression of interest, the investigator will perform an eligibility screening. In addition to meeting the inclusion criteria as outlined above, participants should: i. have available serum from their first post 9/11 WTC-HP ii. Not currently be receiving treatment for malignancy iii. Have no limitations to a minimal risk blood draw iv. Be willing and able to sign consent; and v. be able to attend a single-visit.

All co-investigators have received training from the principal investigator in how to obtain consent and answer questions that may arise during the consent process. The consent and letter have been written to comply with the requirement that they be written at a 5th grade reading level, evaluated by the Flesch–Kincaid readability test. In addition, subject will be asked to provide their understanding of what the study is about at the time of the consenting process. English is the primary language of all FDNY rescue workers, see Appendix.

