### Power analysis

A sample size of 40 cases for each group of GERD, AHR, AHR/GERD overlap, BE, and non-GERD/non-AHR Controls (all will be subsets of AIM 1 *N =* 898 randomly selected cohort) achieves 80% power to detect difference as small as 0.78 SD with two-sample t-test at 0.01 significance level to account for multiple comparisons. This will allow us to achieve 80% power and significance of 0.05, based on prior studies with salivary pepsin test (personal communication with [name] of Peptest), Fig. 2.

*Statistical Analysis* SPSS 28 (IBM) will facilitate database management and statistics. Continuous variables expressed as mean, standard deviation (SD) if normally distributed, and as median, inter-quartile range (IQR) if skewed. Two-sample t-test and ANOVA will compare continuous data. Count and proportions will summarize categorical data and Pearson- χ^2^ will compare categorical data. Multivariate binary logistic regression will estimate biomarker-disease relationship for case status as a binary outcome while adjusting for confounding. Cox proportional hazards model will evaluate the effects of biomarkers, smoking, and exposure on the hazard of developing WTC-GERD or BE over time. The maximum potential effectiveness of a biomarker will be calculated by Youden Index [100]. Goodness of fit, using the Hosmer–Lemeshow test. Survival curves compared by Log-rank test. Pearson χ^2^-test will compare SABA and LABA usage between GERD, AHR, AHR/GERD overlap, BE, and non-GERD or AHR controls. Significance will be assessed by *p <* 0.05 for all statistical tests. Graphs will be created using Prism (v.10, GraphPad Software).

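### Barrett's esophagus (BE) is in practice identified only in men who have had an endoscopy, while GERD-only can be entered without one, so the BE-versus-GERD-only comparison and the BE classifier mix metaplasia with having been scoped

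*Protocol article*

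**What the plan says.** All points are from the protocol article.

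- **BE definition (Case status).** BE is "as a subset of GERD, will have any of the following additional inclusion criteria", namely "biopsy-proven columnar epithelium lining ≥ 1 cm of the distal esophagus with intestinal metaplasia characterized with goblet cells on histology; diagnosis on EMR". The same paragraph, listing the objective routes to GERD, mentions "stricture or Barrett’s esophagus on endoscopy".
- **GERD definition (Case status).** Besides the endoscopic and pH-study routes, "GERD will also be defined on EMR diagnosis and/or PPIs, H_2_ blockers, antacid, or surface agent use". These last routes need no endoscopy.
- **Groups (Study population, recruited cohort).** "We will recruit a subset" of 40 per group, with GERD-only and BE as separate groups. Attendance is at a single visit, and the assessments described for it include no endoscopy.
- **Analysis (Power analysis, Statistical Analysis, Model building).** Groups are compared by t-test and ANOVA. Logistic regression relates biomarkers to case status, with adjustment for confounding in general terms. A boosted-tree classifier is built for AHR, GERD, overlap and BE. A Cox model addresses effects "on the hazard of developing WTC-GERD or BE over time". No endoscopy history is named as a restriction or covariate.
- **Background.** People with endoscopic evidence of reflux may have no symptoms, "potentially leading to under-diagnosis of patients at risk of BE and EAC".

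**The concern.** The two labels rest on different amounts of investigation. A BE label presupposes that someone examined the esophagus. A GERD-only label does not, and the single study visit cannot correct it later. Two separate problems follow.

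1. **Ascertainment.** Men referred for endoscopy are likely to differ from men who simply take an acid-related drug, for example in symptoms or intensity of care. A biomarker that tracks such a difference would separate BE from GERD-only with no link to metaplasia. The direction of this bias is not known.
2. **Dilution.** GERD-only men who were never scoped may have undetected BE. Each one moves the GERD-only mean toward the BE mean and shrinks a true difference.

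Finding noninvasive markers of BE is one of the study's main stated purposes, and GERD without BE is the natural comparator for it.

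**Working it through.** **Inputs.** From Power analysis: 40 per group, difference 0.78 SD, two-sample t-test, alpha 0.01, power 80%. From Statistical Analysis: p < 0.05 for all tests. Three quantities are assumptions, because the documents give none of them:

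- q, the share of GERD-only men with undetected BE;
- s, the share of GERD-only men who were scoped;
- D, the difference in SD units between scoped and unscoped men on a marker unrelated to BE.

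The SD is taken as 1 in every group; the small inflation from mixing subgroups is ignored.

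**Step 1: the plan's own figure.** For n per group the noncentrality is δ = d × √(n/2), with 2n − 2 degrees of freedom. With d = 0.78 and n = 40, δ = 0.78 × √20 = 3.49 on 78 degrees of freedom. Two-sided at alpha 0.01, power is 79.9%, so the stated 80% reproduces. A one-sided test would give 86.5%, so the plan's figure is two-sided. At alpha 0.05 the same design has 93.1%.

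**Step 2: dilution.** If a share q of the GERD-only group has BE, the expected difference is 0.78 × (1 − q).

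| q | Men of 40 | Difference (SD) | Power, alpha 0.01 | Power, alpha 0.05 |
|---|---|---|---|---|
| 0% | 0 | 0.78 | 79.9% | 93.1% |
| 5% | 2 | 0.74 | 74.8% | 90.5% |
| 10% | 4 | 0.70 | 69.0% | 87.3% |
| 20% | 8 | 0.62 | 56.2% | 78.7% |

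**Step 3: ascertainment with no BE effect at all.** Suppose every BE case was scoped. The BE mean then carries the full D and the GERD-only mean carries s × D, so the spurious difference is D × (1 − s). Chance of a significant result with 40 per group:

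| D | s | Spurious difference (SD) | Alpha 0.01 | Alpha 0.05 |
|---|---|---|---|---|
| 0.3 | 0.4 | 0.18 | 3.7% | 12.5% |
| 0.5 | 0.2 | 0.40 | 20.5% | 42.4% |
| 0.5 | 0.4 | 0.30 | 10.3% | 26.3% |
| 0.5 | 0.6 | 0.20 | 4.5% | 14.3% |
| 0.8 | 0.4 | 0.48 | 31.7% | 56.4% |
| any | 1.0 | 0 | 1% | 5% |

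The last row shows why a scoped comparator helps: when both groups were scoped, this source of error disappears.

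**Step 4: precision of a scoped-only comparator.** With 40 BE cases and m scoped GERD-only men, δ = 0.78 × √(40m/(40 + m)) on 38 + m degrees of freedom. If s = 0.6, m = 24, δ = 0.78 × √15 = 3.02, and power is 64.2% at alpha 0.01 (84.5% at 0.05). If s = 0.4, m = 16, δ = 0.78 × √11.43 = 2.64, and power is 49.2% (73.6%).

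**The case against.** - **The premise may be met in text not shown.** The article places study definitions and eligibility criteria in Table 1, which is not visible; nor is Fig. 2. A BE exclusion for the GERD-only group could sit there. This stands as a limit: the point covers only the visible text, which is explicit and adds no such restriction.
- **The record route to BE does not literally name an endoscopy.** True. But a recorded BE diagnosis ordinarily presupposes one, so the asymmetry with drug-defined GERD remains.
- **A reader might infer that the article itself concedes hidden BE in the GERD-only group.** It does not. The Limitations section speaks of people with no GERD history who might prove to have GERD. The Background remark concerns silent reflux in people at risk of BE. It makes missed BE plausible but does not report it in treated GERD.
- **A reader might infer that the event date for BE is the endoscopy date, so that the Cox model is biased.** No text defines an event date. The wording also allows one combined GERD-or-BE endpoint, which many men would reach on entering GERD, before any BE diagnosis. The survival analysis is a problem only if BE is modelled as its own outcome.
- **The figures are assumed.** This stands. The 0.78 SD is a generic detectable difference, not an expected BE effect, and at alpha 0.05 the dilution loss leaves power near 80% even at q = 20%.
- **Adjustment for confounding is planned, and covariate lists belong in an analysis plan.** Partly fair. But adjustment cannot reclassify undetected BE, and it needs endoscopy history to have been collected.

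**Conclusion.** The point holds for the BE-versus-GERD-only comparison and the BE classifier. On the visible definitions, one group has in practice been examined for BE and the other need not have been, so a difference between them cannot be attributed to metaplasia alone.

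Neither the size nor the direction of the net bias can be derived from the documents. Dilution costs between about 5 and 24 percentage points of power at alpha 0.01 for q from 5% to 20%, and between about 3 and 14 points at alpha 0.05. Ascertainment could raise the false-positive rate at alpha 0.01 from 1% to between 3.7% and 31.7% for D from 0.3 to 0.8 with 40% of GERD-only men scoped. These ranges rest wholly on the assumed q, s and D. The plan's own power arithmetic is not in error. The change is worth making before analysis, but the point does not invalidate the study.

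**What to change.** Extract the date and result of prior endoscopies from the medical record that the study already uses for clinical variables. For the BE comparisons and the BE classifier, prespecify an analysis whose comparator is GERD-only men with a documented post-9/11 endoscopy without BE. Report it beside the analysis with all GERD-only men, and state how many in that group were scoped.

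Leave recruitment order unchanged. Approaching scoped men first would make the GERD-only group unrepresentative for its comparisons with AHR, overlap and controls, and would move it away from the unscoped people a noninvasive test is meant for.

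If BE is modelled as a separate time-to-event outcome, describe its date as a date of detection and include endoscopy history up to each time point as a time-dependent covariate. Do not restrict that cohort to men ever scoped, since that would condition on something that happens during follow-up.

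**Cost.** Record abstraction and some analysis wording, with no new procedure, provided that endoscopy dates and results are retrievable; the article does not list them among the variables extracted. The scoped comparator will be smaller and more intensively investigated. As step 4 of the working shows, the loss of precision can exceed the loss from dilution, which is why both analyses should be reported.

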**Table 2 Tab2:**
[figure not shown]
Schedule of study related activities

*FeNO* Fractional Exhaled Nitric Oxide, *EBC* Exhaled Breath Condensate, *SF-36* Short-Form 36, *HRQL* Health-Related Quality of Life, *SGRQ* St. George’s Respiratory Questionnaire, *PAGI-SYM* Patient Assessment of Upper Gastrointestinal Disorders- Symptoms Severity, *PAGI-QoL* Patient Assessment of Upper Gastrointestinal Disorders- Quality of Life, *MOCA* Montreal Cognitive Assessment, *MMSE* Mini Mental State Examination

^*^Consent and questionnaires may be obtained in person if subjects prefer

^**^Samples collected prior to in person visit

**Table 3 Tab3:**
[figure not shown]
Endpoints of the BADBURN trial

*TNF-α* Tumor Necrosis Factor, *C peptide* Connecting peptide, *IP-10* Interferon-gamma-induced protein 10, *FEV1* Forced Expiratory Volume in 1 s, *EBC* Exhaled Breath Condensate, *FeNO* Fractional Exhaled Nitric Oxide, *SGRQ St.* George’s Respiratory Questionnaire, *GERD* Gastroesophageal Reflux Disease, *PAGI-SYM* Patient Assessment of Upper Gastrointestinal Disorders- Symptoms Severity, *PAGI-QOL* Patient Assessment of Upper Gastrointestinal Disorders- Quality of Life, *SF-36* Short-Form 36, *HRQL* Health-Related Quality of Life measures, *MOCA* Montreal Cognitive Assessment, *MMSE* Mini-Mental State Examination

### Measurement visit

Participant demographic information, medical history and medication history will be obtained. A physician will perform the physical examination, and verify that inclusion/exclusion criteria are met. Enrolled participants will undergo the following assessments.

### Blood sampling

After at least an 8 h fast, serum and plasma will be obtained, aliquoted and banked. Each stored specimen will be assigned a unique code to ensure proper identification and linkage to the respective participant. Aliquots from the fresh samples will be assayed for complete blood count (with differential) and chemistry panel. These data are already available for the banked samples. For all samples, lipid profile, metabolomics, and protein biomarker profiling will be performed [10, 28–30, 76, 77].

### Salivary pepsin assessment

30 mL sterile plastic tubes with 0.5 ml of 0.01 M citric acid, adjusted to a pH of 2.5 (RD Biomed Ltd., Hull, UK), will be used by the participants to collect saliva in the AM (prior to brushing teeth, drinking or eating), 1 h after finishing lunch, and 1 h after finishing dinner [78, 79]. Participants will be instructed to cough a few times prior to spitting into the tube to clear saliva from the back of the throat and then spit into the tube. The collected samples will be stored at 4 °C and analyzed within 2 days. Salivary Pepsin will be analyzed using Peptest (RD Biomed Ltd., Hull, UK) as previously described [79]. Briefly, plastic tubes will be centrifuged at 4,000 rpm for 5 min, and 80μL of supernatant will be added to 240μL of migration butter solution for 10 s. 80μL of the mixture will be added to the well of the Peptest, which contains two unique human monoclonal antibodies that detect and capture pepsin protein (specific to pepsin-3), with a lower limit of detection of 16 ng/mL and an upper limit of 500 ng/mL. A salivary pepsin level of ≥ 16 ng/mL will be considered positive. The sample will be processed in a Pepcube reader to quantify the pepsin concentration [78].

*Spirometry* will be assessed using a KoKo PFT spirometer (nSpire Health Inc)**,** and lung function assessment will be considered acceptable as per the ATS/ERS guidelines [80]. We will select the largest acceptable measures for electronic archiving. Each participant’s predicted percentage (%) will be calculated by NHANES III equations based on their age at examination, height, sex, and race [80, 81].

*FeNO* will be quantified using NIOX VERO® (Aerocrine) [82, 83]. Participants will be instructed to inhale to their total lung capacity via mouthpiece for 2–3 s. Then, they will exhale at a flow rate of 0.05L/second. The device will provide results in parts per billion (ppb).

*Exhaled breath condensate (EBC)* will be collected using RTubes (Respiratory Research, Inc., USA) [84]. Approximately 1-2 mL of EBC sample will be obtained after 10 min of quiet normal breathing [85]. *PH measurement.* EBC pH assay is extremely simple to perform, inexpensive, and robust, and can be easily processed on the day of collection [86]. EBC will be de-aerated of CO_2_ by bubbling free argon gas (350 ml/min) under a micro-pH reader (Orion PerpHecT micro-pH electrode) and stabilized pH will be recorded after approximately 3–5 min [87]. Aliquots are then stored at -80⁰C and thawed only once prior to histamine and biomarker assessment.

### Naso/oropharyngeal microbiome

#### Collection

Trained study team members will collect naso/oropharyngeal samples using commercially available kits (OMR-110 by DNA Genotek, Canada). Each naris will be swabbed in a circular fashion 10 times. The oropharyngeal sample will be collected by swabbing in the back of the throat in 10 circular motion to ensure sufficient swab collection. Each absorbent swab will be placed into a vial containing 1 mL of stabilizing liquid using aseptic technique. The sample will be treated with lyophilized Proteinase K, and incubated in the original vial at 50⁰C for 1 h in a water bath prior to aliquoting for long-term storage at -80⁰C.

### Quality of life, aerodigestive disease and end-organ effect questionnaires

*Gastrointestinal impact* will be assessed using with the Patient Assessment of Upper Gastrointestinal Disorders – Quality of Life (*PAGI-QoL*) and the Patient Assessment of Upper Gastrointestinal Disorders Symptom Severity Index (*PAGI-SYM*). Both questionnaires use a 6-point Likert scale (MAPI Research Trust) [88–91].

*Respiratory and QoL assessment* will utilize the Health-Related Quality of Life measures (*HRQL*) [92], St. George’s Respiratory Questionnaire (*SGRQ*), and the Short-form-36 (*SF-36*). HRQL assesses an individual's perceived physical and mental health. The SGRQ is a standardized, self-administered airways disease-specific questionnaire divided into three subscales- symptoms, activity, and impact [93]. SF-36 will capture supplemental information about their mental health, general health perception, emotional, and social role functioning [94].

*Cognition* will be assessed using the Montreal Cognitive Assessment (*MoCA*; version 8.1) and the Mini-Mental State Examination (*MMSE*). MMSE is a cognitive test used to evaluate early dementia [95, 96]. Combining MoCA and MMSE can improve diagnostic utility [97]. The MoCA will be administered by a trained/certified investigator. Members of our research team have completed MoCA training and certification through a validated MoCA cognition portal [98] (https://mocacognition.com/). Similar to the MoCA, the MMSE assesses orientation, memory, visuospatial and language domains. Additionally, the MMSE evaluates comprehension, reading and writing [99]. The PI will thoroughly review all scores.

### Outcomes

Levels of salivary pepsin, pH Levels from EBC, Histamine Concentration from EBC, Score on PAGI-QOL Questionnaire, Score on PAGI-SYM Questionnaire, Score on SGRQ-C Questionnaire, and SF-36.

### Power analysis

A sample size of 40 cases for each group of GERD, AHR, AHR/GERD overlap, BE, and non-GERD/non-AHR Controls (all will be subsets of AIM 1 *N =* 898 randomly selected cohort) achieves 80% power to detect difference as small as 0.78 SD with two-sample t-test at 0.01 significance level to account for multiple comparisons. This will allow us to achieve 80% power and significance of 0.05, based on prior studies with salivary pepsin test (personal communication with [name] of Peptest), Fig. 2.

*Statistical Analysis* SPSS 28 (IBM) will facilitate database management and statistics. Continuous variables expressed as mean, standard deviation (SD) if normally distributed, and as median, inter-quartile range (IQR) if skewed. Two-sample t-test and ANOVA will compare continuous data. Count and proportions will summarize categorical data and Pearson- χ^2^ will compare categorical data. Multivariate binary logistic regression will estimate biomarker-disease relationship for case status as a binary outcome while adjusting for confounding. Cox proportional hazards model will evaluate the effects of biomarkers, smoking, and exposure on the hazard of developing WTC-GERD or BE over time. The maximum potential effectiveness of a biomarker will be calculated by Youden Index [100]. Goodness of fit, using the Hosmer–Lemeshow test. Survival curves compared by Log-rank test. Pearson χ^2^-test will compare SABA and LABA usage between GERD, AHR, AHR/GERD overlap, BE, and non-GERD or AHR controls. Significance will be assessed by *p <* 0.05 for all statistical tests. Graphs will be created using Prism (v.10, GraphPad Software).

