### Microbiome of the gut/lung axis

Asthma susceptibility is influenced by the gut microbiome [106–111]. Noninvasive collection sites that can approximate the pulmonary environment are of key interest. Studies have failed to show that the microbiomes of induced sputum were similar to the lung [112, 113]. Noninvasively collected oropharyngeal and nasopharyngeal swabs in conjunction could approximate the lung microbiome [114]. Research has revealed that the esophageal microbiome undergoes alteration in individuals with GERD, BE, and other motility disorders [115, 116]. Although these findings highlight the potential role of the microbiome studies in the diagnosis and therapeutic approaches for aerodigestive disease, further studies are needed and will be one of the key readouts planned in our study.

*EBC* analysis holds great promise in addressing unmet medical needs by expanding the portfolio of noninvasive assays for the multiple coexisting pathological mechanisms underlying respiratory disorders and GERD. Compounds identified in EBC include histamine, adenosine, ammonia, hydrogen peroxide, isoprostanes, leukotrienes, nitrogen oxides (NOx), peptides, cytokines, protons and various ions [85]. Histamine plays a vital role in digestion but elevated levels can contribute to the development of GERD [117, 118].

*Salivary pepsin* has been studied in several GERD biomarker studies [105]. Due to the overlap of various reflux symptoms with other GI pathologies, the diagnosis of GERD can be challenging. However, salivary pepsin test offers a simple and convenient way for detecting reflux through salivary sample collection, providing quick and non-invasive results. Compared to other diagnostic modalities, this approach is time-efficient and requires much less effort [119]. Moreover, pepsin measurements can identify pathologic reflux even in the absence of symptoms, and remain unaffected by the concurrent use of PPI. Several studies have demonstrated that pepsin detection in the sputum and/or saliva can be regarded as a sensitive, non-invasive method for the diagnosis of the proximal reflux of gastric contents, with a sensitivity ranged from 41.5% to 73% and high specificity of 86.2 to 98.2% [78, 79]. Despite these findings little is known about pepsin in the context of aerodigestive co-morbid disease.

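### The group size of 40 is tied to salivary pepsin and a t-test in SD units, but most controls would read below the assay's detection limit, so the 80% power need not carry over to a raw-scale t-test on pepsin

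*Protocol article*

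**What the plan says.** **Sample size.** The Power analysis section sets "A sample size of 40 cases for each group of GERD, AHR, AHR/GERD overlap, BE, and non-GERD/non-AHR Controls". It states that this "achieves 80% power to detect difference as small as 0.78 SD with two-sample t-test at 0.01 significance level", the 0.01 being there for multiplicity. The next sentence repeats 80% power, now with significance at 0.05, and says this is "based on prior studies with salivary pepsin test", sourced to a personal communication. No pepsin mean, SD or distribution is given.

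**Outcome.** The Outcomes section lists "Levels of salivary pepsin" first among several outcomes that are not ranked.

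**Assay.** The Salivary pepsin assessment section describes an assay "with a lower limit of detection of 16 ng/mL and an upper limit of 500 ng/mL", and adds: "A salivary pepsin level of ≥ 16 ng/mL will be considered positive". Saliva is collected three times in the day.

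**Accuracy.** The salivary pepsin paragraph of the Discussion (under the microbiome heading) reports pepsin detection "with a sensitivity ranged from 41.5% to 73% and high specificity of 86.2 to 98.2" per cent. It cites the same two references as the assay method.

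**Analysis.** For continuous data the Statistical Analysis paragraph names only the two-sample t-test and ANOVA. Skewness changes the summary to median and IQR but not the test. Pearson chi-square is named for categorical data, and every test is to be judged at 0.05.

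**The concern.** The positivity cut equals the detection limit, so a negative result is a reading with no number attached. With specificity of 86–98%, nearly the whole control group would sit at one unquantified value. The mean, SD and t-test for that group then depend on whatever is substituted for a reading below 16 ng/mL and on a few high readings. A difference in SD units has no settled meaning on such data until the substitution rule is fixed, and the article's own pepsin figures do not lead to 0.78 SD.

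Two things are at stake: whether the 80% can be read as a statement about pepsin, the marker the sample size is tied to, and whether the named test wastes information that a rank or positive/negative comparison of the same readings would keep.

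**Working it through.** **1. The plan's figure.** Two-sided two-sample t-test, 40 per group, 0.78 SD, alpha 0.01, noncentral t: power 79.9%, with a smallest detectable difference of 0.781 SD. The stated 80% reproduces. At alpha 0.05 the same inputs give 93.1%.

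**2. Readings below the limit, from the article's accuracy range, per 40 people**
- Controls (specificity × 40): 0.862 × 40 = 34.5 to 0.982 × 40 = 39.3.
- GERD cases ((1 − sensitivity) × 40): 0.27 × 40 = 10.8 to 0.585 × 40 = 23.4.

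Positive rates are therefore 13.8% or 1.8% in controls and 41.5% or 73% in cases.

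**3. Power for GERD versus control, 40 per group.** The Pearson figures come from full binomial enumeration and need no distributional shape. The t-test and Mann-Whitney figures are simulated (20,000 and 4,000 runs) under these assumptions: one reading per person; log-normal pepsin with log-SD 1, 1.5 or 2, calibrated to the positive rates; values below 16 entered as 0 or 8 for the t-test and tied for the rank test; values capped at 500. Ranges run over log-SD and substitution value, with simulation error of about one percentage point.

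| Cases / controls positive | Alpha | Raw t-test | Mann-Whitney | Pearson |
|---|---|---|---|---|
| 41.5% / 13.8% | 0.01 | 24–52% | 62–64% | 61% |
| 41.5% / 13.8% | 0.05 | 61–79% | 83–85% | 81% |
| 41.5% / 1.8% | 0.01 | 62–94% | 99% | 99% |
| 41.5% / 1.8% | 0.05 | 95–99% | over 99% | over 99% |
| 73% / either | 0.01 | 98% or more | over 99% | over 99% |
| 73% / either | 0.05 | over 99% | over 99% | over 99% |

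In the first scenario the standardised difference on the recorded values is 0.44–0.55 SD, not 0.78. Entering 8 instead of 0 alone moves t-test power at 0.01 from 52% to 43% (log-SD 1).

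**4. Variants**
- *Log scale:* a t-test on log pepsin, with 8 substituted, gives 62–65% at 0.01 in the first scenario (log-SD 0.5 to 2), close to the rank test.
- *0.78 SD on the recorded values:* if the recorded means really differ by 0.78 of the recorded SD, simulated t-test power is 84–98%.
- *0.78 SD on the underlying log scale, before the detection limit acts:* power is 18–52% at specificity 86.2% and 1–4% at 98.2%. The meaning of 0.78 SD therefore depends on a scale the article does not name.
- *False positives:* with no true difference, the simulated rejection rate of the raw t-test stays below the nominal 1% (0.7% or less). The cost is power, not type I error.

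**5. Three samples.** If the accuracy figures are per sample and the samples are independent (both assumptions, and favourable), the share of controls with all three below the limit is 0.862³ = 64% to 0.982³ = 95%, still a majority. Any-positive rates in the least favourable scenario become 1 − 0.862³ = 36% and 1 − 0.585³ = 80%. Pearson power at 0.01 is then 94%.

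**The case against.** A reader might infer from the least favourable row that the study is underpowered, or that pepsin power is simply 61%. The documents do not support either reading, for these reasons:

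- **Alpha.** The sentence that mentions pepsin carries 0.05, not 0.01. At 0.05 the positive/negative comparison reaches 81% even in the worst scenario, and only the raw t-test falls short. This stands, and any figure quoted at 0.01 alone would mislead.
- **Three readings.** One reading per person is a modelling choice. Under independence, combining three raises worst-case power at 0.01 to 94% (Pearson, any positive) and 88–98% (raw t-test on the three-sample mean). This stands as a limit on the low figures. Independence within one person on one day is the most favourable extreme.
- **Transferred accuracy.** The Discussion's figures cover sputum and/or saliva and proximal reflux, with no cut-off stated, while the Case status section defines GERD broadly, including by medication use. Applying them here is an assumption. The shared references with the assay method make it reasonable but do not prove it.
- **Existing tools.** The cut-off and the chi-square test are already in the article, and so is logistic regression of case status on biomarkers. This makes the remedy cheap, but the only tests named for comparing levels are still t-test and ANOVA.
- **Left to a fuller document.** Coding of values below the limit could be. The test, the effect size, the power and the link to pepsin are stated in the article, so they can be judged here.

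**Conclusion.** The point holds in limited form and is of moderate weight. The 80% at 0.78 SD is correct arithmetic for an uncensored continuous marker. The article does not show that it applies to pepsin: it gives no pepsin mean or SD, and its own assay limit and accuracy range imply that most controls have no numeric value. A raw-scale t-test on such data depends on an unstated substitution value. At 41.5% sensitivity it also gives up power: at alpha 0.01, about 24–52% against 61–64% for the alternatives at specificity 86.2%, and 62–94% against 99% at specificity 98.2%.

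The shortfall is not general. It vanishes at 73% sensitivity and shrinks at alpha 0.05 or if three samples are combined favourably. All figures below 80% rest on a single reading per person and on the accuracy range applying to these groups at 16 ng/mL. The t-test and rank figures also need the log-normal shape. The accuracy range bears only on GERD versus control, and nothing here speaks to power between the disease groups.

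**What to change.** 1. In the Statistical Analysis paragraph, compare pepsin levels by a rank test with all readings below 16 ng/mL tied at the bottom and all above 500 ng/mL tied at the top, or by a Tobit model. Compare the proportion positive at the existing cut by the Pearson chi-square test already named.
2. State how the three daily samples form one value per participant, for example any positive or a prespecified summary.
3. In the Power analysis section, say whether 0.01 or 0.05 applies to pepsin. Give its power as a range under stated assumptions: for a single reading and the Pearson test, about 61% to over 99% at 0.01, or about 81% to over 99% at 0.05.
4. Keep the 0.78 SD statement for continuous markers that are not censored.

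The cost is a few sentences and no new data or participants. The downside is slightly more analysis text and a less favourable power figure at the low end.
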